## 3. Statistical Analyses

Chi-squared tests and *t*-tests will be performed for the categorical and continuous variables, respectively, to examine the presence of any group differences in the demographics and clinical profiles between the treatment and sham groups at baseline. A two-way analysis of variance (ANOVA) with repeated measures will be used to examine the effect of time and treatment conditions on the CARS scores and other secondary outcomes across various assessment time points. Post hoc analyses will also be performed using Bonferroni corrected *t*-tests to investigate the improvements in all outcome variables in pairwise comparisons across various assessment time points. The level of statistical significance will be set at a *p* value < 0.05. Intention-to-treat last-observation-carried-forward scores will be used for the analyses. Missing data will be managed by multiple imputation. All computations will be performed using SPSS for Windows, version 25.0.

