### 1.2. Hypotheses

#### 1.2.1. Primary Hypothesis

Participants in the verum TPS group will have a significant reduction in Childhood Autism Rating Scale (CARS) score at posttreatment compared with the sham TPS group and be maintained at the 1-month and 3-month follow-ups.

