## 2. Materials and Methods

### 2.1. Trial Design

This proposed study is a two-armed, randomized, double-blind, sham-controlled trial evaluating the efficacy and tolerability of a 2-week TPS treatment on ASD among adolescents. This study’s trial design strictly complies with the Consolidated Standards of Reporting Trials (CONSORT) statement [9] and Good Clinical Practice. Participants will be randomly allocated into the verum TPS group or sham TPS group. All the participants’ parents will be informed about the randomization procedures and that they have a 50% chance of receiving the verum TPS or the sham TPS. This study will be conducted in accordance with the Declaration of Helsinki [10]. Both groups will be measured at baseline (T1), immediately after the 2-week intervention (T2), and at 1-month (T3) and 3-month (T4) follow-ups [11] (Figure 1). We registered this trial with ClinicalTrials.gov on 7 June 2022 (NCT05408793).

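### Two missing-data rules, LOCF and multiple imputation, are prescribed without scope or priority, and LOCF can overstate maintenance of the CARS effect for participants lost after T2

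*Protocol article*

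**What the plan says.** Section 3 (Statistical Analyses) first names the model: "A two-way analysis of variance (ANOVA) with repeated measures will be used to examine the effect of time and treatment conditions on the CARS scores", with the secondary outcomes treated the same way. It then states, in two consecutive sentences, "Intention-to-treat last-observation-carried-forward scores will be used for the analyses. Missing data will be managed by multiple imputation". Neither sentence is limited to an outcome, a visit, a kind of missingness (missed visit or missing item), or a primary or sensitivity role. No other section of the article settles this.

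The visits are fixed in section 2.1: "Both groups will be measured at baseline (T1), immediately after the 2-week intervention (T2), and at 1-month (T3) and 3-month (T4) follow-ups". Section 1.2.1 makes persistence part of the primary hypothesis: the CARS reduction is to be shown "compared with the sham TPS group and be maintained at the 1-month and 3-month follow-ups".

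**The concern.** A classical repeated-measures ANOVA needs a value at every visit, so the missing-data rule decides what enters the primary analysis. For a missed CARS visit the two sentences give different answers. LOCF inserts the participant's last score. Multiple imputation draws values from a model and carries the uncertainty into the pooled result. An analyst reading section 3 cannot tell which to use.

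LOCF also bears directly on the hypothesis. A participant seen at T2 and then lost is given T3 = T4 = T2, which is what "be maintained at the 1-month and 3-month follow-ups" asserts. In a T2-to-T4 comparison, each such participant contributes a change of exactly zero, so any true waning shrinks in proportion to the loss.

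At stake are the T3 and T4 conclusions on CARS, and on the secondary clinical measures that have their own maintenance hypothesis. With 17 per arm, the choice of rule can also change whether a result is significant.

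**Working it through.** **Inputs from the article.** 17 per arm, 34 in total, and an effect size of 0.5 (section 2.5); visits T1 to T4 (section 2.1); "The level of statistical significance will be set at a *p* value < 0.05" (section 3), taken as two-sided. No dropout rate, power or effect-size metric is given.

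**The plan's own figure.** No number in the plan concerns missing data. The sample size helps to choose plausible effects. If 0.5 is Cohen's f, then for two equal groups d = 2 × 0.5 = 1.0, and 17 per arm gives power 0.807 (16 per arm gives 0.781). So 34 is reproduced if 80% power was intended. If 0.5 is a between-arm d, 17 per arm has power 0.29. T2 effects of 0.5, 0.8 and 1.0 SD are therefore shown below. The 0.8 SD value is an assumption between the two readings.

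**Formula.** Let p be the fraction lost after T2, equal in both arms and at random, and let δ2 and δ4 be the true verum-versus-sham effects at T2 and T4. Under LOCF the expected T4 difference is (1 − p) × δ4 + p × δ2, so

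bias at T4 = p × (δ2 − δ4).

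**Overstatement when the T2 effect is completely gone by T4 (δ4 = 0), in SD:**

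| Lost after T2 | δ2 = 0.5 | δ2 = 0.8 | δ2 = 1.0 |
|---|---|---|---|
| 15% | 0.15 × 0.5 = 0.075 | 0.15 × 0.8 = 0.12 | 0.15 × 1.0 = 0.15 |
| 20% | 0.20 × 0.5 = 0.10 | 0.20 × 0.8 = 0.16 | 0.20 × 1.0 = 0.20 |
| 30% | 0.30 × 0.5 = 0.15 | 0.30 × 0.8 = 0.24 | 0.30 × 1.0 = 0.30 |

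Three participants lost in an arm of 17 is 3/17 = 17.6%.

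**When the bias is zero or reverses.**
- Effect truly maintained (δ4 = δ2): bias = p × 0 = 0.
- Loss before T2: baseline is carried, where the expected difference is 0, so bias = −p × δ4. With δ4 = 1.0 and 20% loss, the effect shown is 0.80 SD.
- Delayed effect (δ2 = 0, δ4 = 1.0), 20% lost after T2: bias = 0.20 × (0 − 1.0) = −0.20, again showing 0.80 SD.
- Loss after T3: the T3 score is carried, not the T2 score.

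**Effect on the test.** Simulation assumptions: 17 per arm, SD 1, correlation 0.5 between visits, random loss after T2, two-sided t-test at T4. With complete waning, LOCF rejected in about 6.0% of trials at 20% loss and 7.1% at 30% for δ2 = 0.5. The rates were about 7.1% and 9.9% for δ2 = 0.8, and about 8.5% and 12.3% for δ2 = 1.0. The nominal rate is 5%.

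**The two rules compared.** Multiple imputation used 20 imputations and a regression on arm, baseline and T2, pooled by Rubin's rules, in 1,500 simulated trials per row:

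| T2 effect → T4 effect | Loss | LOCF rejects | Imputation rejects | Verdicts differ |
|---|---|---|---|---|
| 0.5 → 0 | 20% | 6.7% | 3.9% | 4.6% |
| 0.5 → 0 | 40% | 7.7% | 4.0% | 7.4% |
| 1.0 → 0 | 20% | 8.9% | 4.1% | 8.3% |
| 1.0 → 0 | 40% | 21.2% | 3.8% | 20.9% |
| 1.0 → 1.0 | 20% | 79.7% | 69.1% | 13.2% |
| 1.0 → 1.0 | 40% | 82.8% | 57.0% | 28.2% |

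Under imputation the mean T4 effect stayed within about 0.02 SD of zero in the four waning rows. In these scenarios the choice of rule changed the significance verdict in about 5% to 28% of trials.

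**The case against.** The strongest reply is that the two rules can coexist: LOCF for missed visits, and imputation for missing questionnaire items or missing baseline values, which LOCF cannot fill. CARS has 15 items and SRS has 65, so this is a sensible division of labour. It shows that the sentences are not logically impossible to combine. But the article does not state this division, and even under it LOCF would govern the follow-up visits.

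A second reply is that the bias is conditional and, on modest assumptions, small. That is correct. It needs a T2 effect, waning, and loss after T2 together. At 0.5 SD and 15% loss it is about 0.08 SD.

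A third is that section 2.7 keeps the research assistants who analyse the data blind to allocation. This limits choosing the rule by its result. It does not tell a blinded analyst which rule to apply.

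A fourth is that details of imputation models and sensitivity analyses belong in a statistical analysis plan that is not shown. That holds for such details. Here, however, the article itself fixes two rules for the same values without ranking them.

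A reader might also infer that LOCF makes the standard errors too small because filled values are treated as observed. For the between-arm T4 comparison this is not supported. With δ2 = 0.8, δ4 = 0 and the simulation assumptions above, the empirical SD of the estimate and the mean model standard error were both 0.352 at 20% loss and both 0.354 at 30%. With no effect at either visit, rejection was 4.9% to 5.0%. The distortion is bias. The repeated-measures ANOVA itself was not tested.

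**Conclusion.** The point holds in a conditional form. The ambiguity needs no assumption: as written, section 3 does not define a single primary CARS analysis. The LOCF problem depends on how the effect evolves and when participants leave. With complete waning by T4 and 15% to 30% random, equal loss after T2, LOCF overstates the T4 effect by about 0.08 to 0.15 SD for a T2 effect of 0.5 SD, and by 0.12 to 0.24 SD for 0.8 SD. The loss rates, the 0.8 SD effect and the complete waning are assumptions, because the article gives no figures for them.

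Two stronger readings are tempting and should not be drawn. One is that LOCF creates a maintained effect regardless of the data. It does not: as shown above, the bias vanishes for a maintained effect and works against verum for early loss or a delayed effect. The other is that every secondary outcome is affected. Section 1.2.2 states no maintenance hypothesis for the Asperger's scale (ASAS) or working memory, and imaging is done only before and after treatment, so it has no T3 or T4 value to carry forward.

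**What to change.** Replace the two sentences by one primary rule, with all participants analysed in the arm to which they were randomised. Either of these would do:

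- multiple imputation, which the article already names, using baseline and earlier visits, with pooled estimates; or
- a likelihood-based mixed model for repeated measures on all observed visits.

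Both rest on missing-at-random, and the text should say so. Remove LOCF as a primary rule; if it is kept, label it a sensitivity analysis. If imputation is meant only for missing items, state that separately from the rule for missed visits. A sensitivity analysis that departs from missing-at-random is optional.

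The cost is one paragraph of wording and no new data. One consequence should be accepted openly. In the simulation with a truly maintained 1.0 SD effect and 20% loss, imputation had power of about 0.69 against 0.80 with LOCF. The higher figure depends on assuming no change after T2. The rule should be fixed before any outcome data are seen by arm.

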## 4. Conclusions

This study will be the first clinical trial in Hong Kong and nationwide to evaluate the efficacy and safety of TPS on adolescents with ASD. This study will contribute to the development of a new approach to facilitate ASD children in Hong Kong.

## Figures and Tables

**Figure 1 ijerph-19-15614-f001:**
[figure not shown]
CONSORT flow diagram.

## Data Availability

The original contributions presented in the study are included in the article; further inquiries can be directed to the corresponding author.
